# Repetitive vascular occlusion stimulus (RVOS) versus standard care to prevent muscle wasting in critically ill patients (ROSProx):a study protocol for a pilot randomised controlled trial

**DOI:** 10.1186/s13063-019-3547-5

**Published:** 2019-07-24

**Keywords:** Repetitive vascular occlusion stimulus, ICU-acquired weakness, Blood flow restriction, Critical illness, Rehabilitation, Muscle atrophy, Vascular dysfunction

## Abstract

**Background:**

Forty per cent of critically ill patients are affected by intensive care unit-acquired weakness (ICU-AW), to which skeletal muscle wasting makes a substantial contribution. This can impair outcomes in hospital, and can cause long-term physical disability after hospital discharge. No effective mitigating strategies have yet been identified.

Application of a repetitive vascular occlusion stimulus (RVOS) a limb pressure cuff inducing brief repeated cycles of ischaemia and reperfusion, can limit disuse muscle atrophy in both healthy controls and bed-bound patients recovering from knee surgery. We wish to determine whether RVOS might be effective in mitigating against muscle wasting in the ICU. Given that RVOS can also improve vascular function in healthy controls, we also wish to assess such effects in the critically ill. We here describe a pilot study to assess whether RVOS application is safe, tolerable, feasible and acceptable for ICU patients.

**Methods:**

This is a randomised interventional feasibility trial. Thirty-two ventilated adult ICU patients with multiorgan failure will be recruited within 48 h of admission and randomised to either the intervention arm or the control arm. Intervention participants will receive RVOS twice daily (except only once on day 1) for up to 10 days or until ICU discharge.

Serious adverse events and tolerability (pain score) will be recorded; feasibility of trial procedures will be assessed against pre-specified criteria and acceptability by semi-structured interview. Together with vascular function, muscle mass and quality will be assessed using ultrasound and measures of physical function at baseline, on days 6 and 11 of study enrolment, and at ICU and hospital discharge. Blood and urine biomarkers of muscle metabolism, vascular function, inflammation and DNA damage/repair mechanism will also be analysed. The Health questionnaire will be completed 3 months after hospital discharge.

**Discussion:**

If this study demonstrates feasibility, the derived data will be used to inform the design (and sample size) of an appropriately-powered prospective trial to clarify whether RVOS can help preserve muscle mass/improve vascular function in critically ill patients.

**Trial registration:**

ISRCTN Registry, ISRCTN44340629. Registered on 26 October 2017.

**Electronic supplementary material:**

The online version of this article (10.1186/s13063-019-3547-5) contains supplementary material, which is available to authorized users.

## Background

Increasing numbers of patients are being admitted to intensive care units (ICUs) and mortality rates have fallen [1–3]. However, survival comes at the expense of increased dependency and debility: 50% of patients of working age do not return to work; 70% require assistance with daily living activities in the year following discharge; and physical disability can persist for many years [4, 5]. The UK’s National Institute of Health and Care Excellence (NICE) has declared such post-ICU debility to be a public health issue [6].

Impaired quality of life and functional limitation partly result from ICU-acquired weakness (ICU-AW) [7–10]. This affects approximately 40% of adult ICU patients [11], with long-term ventilated or severely septic patients being most commonly and severely affected [12–16]. ICU-AW is associated with poorer outcomes: prolonged mechanical ventilation, increased ICU and hospital length of stay, increased hospital and post-discharge mortality rates, chronic functional disability and reduced quality of life among survivors [8, 17–20]. As a consequence, hospital health-care costs are 30% higher in those affected, with further excess costs relating to the need for rehabilitation, frequent re-admissions and social care upon discharge [18].

The pathophysiology of ICU-AW is multifactorial [10, 21–23]. Whilst neuropathies may occur [24], skeletal muscle wasting plays a central role [25]. The cross-sectional area of the rectus femoris (thigh) muscle (RFCSA) falls by an average of 18% in just 10 days in ventilated ICU patients, and to the greatest degree in those with the largest burden of organ failure [21]. This is underpinned by impaired skeletal muscle protein synthesis and, simultaneously, increased protein breakdown [21, 26], to which altered muscle metabolism [27] and disuse may contribute [23, 28]. The putative role of drugs such as corticosteroids, neuromuscular junction blocking agents and aminoglycoside antibiotics is contested [16, 29–31].

To date, no therapies exist for prevention or treatment of ICU-AW [32, 33]. Early mobilisation and physical activity regimes have proven ineffective [34–38], perhaps because muscle wasting has already occurred. There is thus growing interest in the early application of non-volitional interventions such as neuromuscular electrical stimulation, although proof of benefit remains lacking [38–42].

Application of a repetitive vascular occlusion stimulus (RVOS) shows promise as a mitigating intervention. Repeated inflation/deflation of a blood pressure cuff around a limb to above arterial pressure (~ 200 mmHg) elicits brief bouts (~ 5 min) of limb ischaemia/reperfusion [43]. In healthy subjects, RVOS can improve exercise performance [44–47], whilst vascular occlusion during low-intensity exercise (blood flow restriction exercise) can enhance hypertrophic and strength responses in skeletal muscle [48] of healthy controls [49–52], athletes [53] and the elderly [54–60], and seems to improve physical function and health-related quality of life in patients with inflammatory muscle disease [61–63]. Moreover, RVOS may mitigate against atrophy induced by immobilisation and unloading: patients recovering from ligament reconstruction surgery who received two sessions of RVOS (five cycles of vascular occlusion for 5 min and release for 3 min) to the proximal thigh daily for > 10 days after surgery had 50% less disuse knee extensor muscles mass loss [43]. Similarly, in healthy volunteers with experimentally induced limb immobilisation, RVOS alone or in combination with exercise preserved muscle strength and mass [64, 65].

The mechanism by which RVOS prevents muscle atrophy remains unclear. Application of RVOS enhanced a murine mTOR signalling pathway involved in protein synthesis [66], whilst increased skeletal muscle oxidative capacity is also implicated [67–70].

In addition to impacts on muscle mass, RVOS improves local and systemic endothelial function and microcirculation in healthy controls [71, 72], perhaps through increases in plasma concentration of vascular endothelial growth factor (VEGF) and endothelial progenitor cells [73]. However, it is unknown whether RVOS can prevent or offset macrovascular and microvascular dysfunction observed in bed-rest/ immobilised individuals [74–76] and critically ill patients [77–79].

Of note, such benefits are seen locally (i.e. in the muscle distal to the occlusion), but also *remotely*—in tissue distant from the site of occlusion (so-called ‘remote preconditioning’). RVOS provides protection against myocardial and renal tissue ischaemic injury at the time of vascular intervention or cardiac surgery [80–85]. Unilateral daily arm RVOS over a week improves bilateral vascular function [71], while a longer (300 consecutive days), more frequent (twice daily), protocol improves cerebral perfusion and reduces recurrent strokes by 30% in patients with intracranial arterial stenosis [86]. The mechanism of such remote benefit has yet to be described [87].

Given its remote effects, application of RVOS to a single limb could potentially prevent muscle wasting and vascular dysfunction at both local and remote sites in critically ill patients, thus mitigating against the development of ICU-AW. Evidence suggests that this approach would be safe, with no reports of elevation of muscle damage markers, such as creatinine kinase and myoglobin, and oxidative stress markers, such as lipid peroxide, during blood flow restriction exercise [50, 52, 88, 89]. Moreover, RVOS pre or post exercise seems to be protective against exercise-induced muscle damage [90, 91]. Amongst 12,642 recipients (including healthy subjects, older subjects and individuals with clinical conditions), attributable serious side effects were few: venous thrombus (0.055%), pulmonary embolism (0.008%) and rhabdomyolysis (0.008%) [92]. No negative impact on haemodynamic, haemostatic and inflammatory responses has been observed in healthy young, older and clinical populations [61, 93–95]. In addition to being safe, RVOS also appears well tolerated, with a pain score of 3.6 ± 3.4 (mean ± SD) out of 10 during application to the lower limb in patients with aneurysmal subarachnoid haemorrhage [96].

We thus wish to determine whether the application of RVOS might help maintain muscle mass and improve vascular function in ICU patients. We here describe a trial designed to assess the feasibility of performing such an appropriately-powered study.

## Methods

### Primary objectives

The primary objective of the trial is to determine whether it is safe and tolerable to apply RVOS to a proximal lower limb of ICU patients.

### Secondary objectives

Our secondary objectives are to determine the feasibility of screening; obtaining consent and recruiting; randomising; retaining patients; delivering the trial intervention; performing outcome assessments and collecting data; assessing acceptability for patients, personal consultees (next of kin) and staff; and to determine outcome data characteristics to design a future larger trial.

In addition, we will explore any impacts on measures of muscle mass, quality and function (strength and physical function measures); vascular function; blood and urine biomarkers of muscle metabolism; vascular function; inflammation and DNA damage/repair mechanisms; and clinical outcomes to inform powering of any future prospective trial.

### Study design

ROSProx is a partially blinded interventional feasibility trial with randomisation. Eligible patients will be randomised to an intervention arm or a control arm. Patient randomised to the control arm will receive standard care, while intervention patients will receive RVOS treatment in addition to all other standard care. The study protocol has been developed in accordance with the Standard Protocol Items: Recommendations for Interventional Trials (SPIRIT) guidelines (see Additional file 1 for the SPIRIT checklist). The study flow diagram is shown in Fig. 1.

**Fig. 1 Fig1:**
[figure not shown]
Study flow diagram. ICU intensive care unit, SOFA Sequential Organ Failure Assessment

### Study setting

The study will take place within the ICUs of two hospitals in England: Royal Surrey County Hospital NHS Trust (RSCH); and Ashford and St Peter’s Hospital (ASPH) NHS Trust.

### Sample size rationale

A total of 30 participants is recommended for pilot and feasibility trials [97]. To allow for balance in the stratification factors (gender and study site), a sample size of 32 participants was chosen, which will allow us to estimate a failure to deliver RVOS in the intervention arm of 30% to within a 95% confidence interval of ± 15.9%.

Based on an anticipated average rate of recruitment of 6 patients/month, 50% screening failure due to weekends, 20% decline of consent and 30% death before trial completion, we aim to recruit 1.6 patients per site per month. Recruiting from two sites, one starting 2 months after the other, is expected to yield 47 patients over 16 months. Recruitment will continue until 32 ICU survivors have been studied (16 patients in each group).

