### Recruitment and randomisation process

All sequential ICU admissions will be screened for eligibility. Eligible patients with mental capacity for informed consent will be approached, the risks and benefits of participation explained and written informed consent will be obtained before enrolment by the investigator physician. However, we envision that the majority of eligible patients will be receiving invasive mechanical ventilation and requiring sedation, and thus lacking capacity to consent. In this instance, declaration of agreement will be sought from the patient’s ‘Personal Consultee’ who may be a representative, partner or close friend. Once the participant recovers and is capable of understanding the details of the trial, they will be approached to provide their informed consent retrospectively. If the patient chooses to withdraw from the trial, they will be given the choice of having their existing data and samples destroyed or excluded from final analysis.

Upon informed consent or declaration of agreement, eligible patients will be randomised to either the intervention arm or the control arm in a 1:1 ratio. Separate randomisation lists have been prepared for each site by an independent statistician and uploaded to the study electronic data capture system PROMASYS (Surrey Clinical Trials Unit). In addition, the randomisation list and corresponding envelopes containing randomisation assignments will be stored in the trial file. Randomisation, outcome measure assessments and RVOS intervention will be performed by a research assistant unblinded to patient allocation.

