### Secondary outcome measures

#### Feasibility

Table 3 presents the pre-specified feasibility criteria that will be assessed.

**Table 3 Tab3:** Feasibility criteria of the study

Trial process	Outcome measure	Feasibility criteria
Screening	Percentage of potentially eligible patients being missed	< 55% of potentially eligible patients being missed
Consent	Percentage of personal consultee/participants agreeing to enrolment	> 75% of personal consultees/participants agreeing to enrolment
Recruitment rate	Number of patients recruited	Recruit 30 patients within 16 months
Randomisation	Demographic and severity of illness in the intervention and control arms	Balanced demographic and severity of illness in intervention and control arm participants
Delivery of intervention	Percentage of RVOS sessions performed out of the total possible sessions	80% of the scheduled RVOS sessions performed
Retention rate	Percentage of patients that remain on the ICU for the full 10 days of study enrolment	> 50% of enrolled patients remain on the ICU for the full 10 days of study enrolment
Outcome measure assessments	Percentage of outcome measure assessments performed within 24 h of the scheduled time Percentage of quality-of-life questionnaires completed at 90-day follow-up	100% of RFCSA ultrasound measurements performed within 24 h of the scheduled time > 75% of vascular, strength and functional capacity measures performed within 24 h of the scheduled time > 75% of surviving patients complete the quality-of-life questionnaires at 90-day follow-up
Electronic case report form data collection	Percentage of missing outcome and clinical data	< 10% missing outcome data including ICU and hospital length of stay and survival < 10% missing clinical data obtained from clinical medical notes and electronic patient records, such as severity of illness scores and requirement for organ supportive therapies

*ICU* intensive care unit, *RFCSA* rectus femoris cross sectional area, *RVOS* repetitive vascular occlusion stimulus

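### The ±15.9% precision stated for RVOS delivery failure uses both arms; with the 16 intervention patients it is about ±22.5%

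*Protocol article*

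**What the plan says.** In the Protocol article, *Sample size rationale* starts from a recommended 30 participants for pilot and feasibility trials. To allow for balance on gender and site, "a sample size of 32 participants was chosen". The section then says that this number makes it possible to "estimate a failure to deliver RVOS in the intervention arm of 30% to within a 95% confidence interval of" ±15.9%.

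The same section fixes the split between arms: "Recruitment will continue until 32 ICU survivors have been studied (16 patients in each group"). *Recruitment and randomisation process* agrees: "eligible patients will be randomised to either the intervention arm or the control arm in a 1:1 ratio". *Study design* gives controls standard care only, and the *Discussion* adds that they receive no sham cuff inflation.

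Delivery of the intervention is also a feasibility criterion. Table 3 (under *Feasibility*) sets it as "80% of the scheduled RVOS sessions performed".

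**The concern.** The precision statement is limited, in its own words, to the intervention arm. A control patient has no RVOS sessions scheduled and so cannot contribute a success or a failure of delivery. The denominator should therefore be the number of patients in the RVOS arm, which is half of the 32. The printed figure looks too small for that number.

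This is the only precision statement in the sample size section. It concerns delivery of the intervention, one of the pre-specified feasibility criteria that feed the decision on a larger trial. A reader who relies on ±15.9% would credit the delivery estimate with twice the information that 16 patients give.

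**Working it through.** **Inputs**

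- Expected failure proportion p = 0.30, 95% confidence, stated half-width 15.9%: *Sample size rationale*.
- Total 32 ICU survivors, 16 per group: *Sample size rationale*.
- 1:1 allocation: *Recruitment and randomisation process*.
- No RVOS and no sham in controls: *Study design* and *Discussion*.
- 30% deaths and 47 expected recruits: *Sample size rationale*. These are used only for the second basis in step 3.

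**Formula.** Normal-approximation half-width for one proportion: 1.96 × √(p(1 − p)/n).

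**1. Reproducing the plan's figure**

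- n = 32: 1.96 × √(0.21/32) = 0.1588, or ±15.9%. This matches the article.
- Solved for n at ±15.9%: 1.96² × 0.21/0.159² = 31.9.

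The figure therefore corresponds to all 32 participants.

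**2. Intervention arm, 16 patients, each counted as delivered or not**

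- n = 16: 1.96 × √(0.21/16) = 0.2245, or ±22.5%.
- Interval around 30%: 7.5% to 52.5%, instead of 14.1% to 45.9%.
- Ratio of widths: √(32/16) = 1.41, so the interval is 41% wider than stated.

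Other methods at n = 16 and p = 0.30 do not recover the printed figure. The Wilson half-width is ±20.5% (13.3% to 54.4%), the t quantile gives ±24.4%, the continuity-corrected half-width is ±25.6%, and even a 90% normal interval is ±18.8%. For whole patients, the exact 95% interval is 7.3% to 52.4% for 4 of 16 and 11.0% to 58.7% for 5 of 16.

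**3. All patients randomised to RVOS**

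Recruitment runs until there are 32 ICU survivors. If 30% die before then, 32/0.7 = 45.7, so about 46 are enrolled, or 23 per arm. The article's 47 gives 47/2 = 23.5 per arm.

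- n = 23: 1.96 × √(0.21/23) = 0.1873, or ±18.7%.
- n = 24: 1.96 × √(0.21/24) = 0.1833, or ±18.3%.

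That is about ±18.5%, still wider than stated. Treating the 30% as deaths in the ICU is an assumption, since the article describes it as death before trial completion. With fewer ICU deaths, fewer patients would be enrolled and the half-width would lie between this value and ±22.5%.

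**The case against.** The arithmetic has no good defence: nothing elsewhere in the article repairs the denominator. The serious objections concern how far the point reaches, and most of them stand.

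- **±22.5% is not the only defensible figure.** The article does not define a delivery failure. The ±22.5% holds for 16 ICU survivors each counted yes or no. Counting patients who die in the ICU gives about ±18.5%. This stands, so both figures are given.
- **The figure might be a session-level calculation.** Table 3 counts sessions. Assume the maximum of 19 sessions (1 + 2 × 9) for each of 16 patients. The half-width is then about ±5% with no within-patient correlation, 13.0% at an assumed correlation of 0.3, 16.3% at 0.5 and 22.5% at 1. It would equal 15.9% near 0.47. A reader might infer that a session calculation is ruled out by these numbers, but they bracket the printed figure and do not exclude it. The case for n = 32 is that it matches directly, the sentence ties the figure to 32 participants, and the article mentions no correlation.
- **A 30% failure rate might seem to contradict the 80% criterion.** It does not. The 30% is a planning value for precision, nearer 50% than 20% is, so it gives the wider interval. Table 3's 80% is a point criterion that counts sessions.
- **The article might seem to claim that the trial can tell 14% failure from 46%.** It makes no such claim. An interval of 14% to 46% says only what an observed 30% would be compatible with.
- **The sample size might seem to fall with the figure.** The number 32 comes from a recommended pilot size and stratification balance, and the precision is stated as a consequence. Delivery is a secondary outcome, the analysis is declared exploratory, and *Trial status* reports recruitment complete. The error therefore does not invalidate the sample size.

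**Conclusion.** The point holds as an error in a stated figure. The ±15.9% is the half-width for 32 patients, while the sentence describes an estimate that only the intervention arm can supply. With patients counted yes or no and the normal approximation at 30% failure, the figure is about ±22.5% for the planned 16, or about ±18.5% for the 23 to 24 expected to be randomised to RVOS. Reaching ±15.9% on this basis would take about 32 patients in the RVOS arm.

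The conclusion rests on the stated 1:1 split and on controls receiving no RVOS. The second figure also rests on the assumed 30% ICU mortality. Neither binomial figure applies to a session percentage or to a mean of per-patient percentages, whose precision depends on how delivery varies between patients.

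**What to change.** In *Sample size rationale*, replace ±15.9% with about ±22.5% for 16 RVOS patients, or with about ±18.5% if all patients randomised to RVOS are counted. State which patients are counted.

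When results are reported, give the observed delivery result with a confidence interval based on the intervention arm only. If the result is Table 3's percentage of sessions performed, the interval should allow for repeated sessions within the same patient.

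The cost is a correction of wording and one reporting choice. The stated precision becomes less favourable. No extra patients are needed, and the rationale for 32 is otherwise unchanged.

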## Discussion

This study will be the first to assess the safety, tolerability, feasibility and acceptability of RVOS in ICU patients. The effect of RVOS on muscle mass atrophy and weakness, and on arterial dysfunction observed in ICU patients, will also be explored.

Thirty-two ventilated critically ill patients with at least two other organ failures will be recruited to the study. Multiple organ failure patients were chosen as the study population because these patients undergo more pronounced muscle wasting (16% decrease in the RFCSA compared to 3% in single organ failure patients within 7 days of ICU admission) [21].

RVOS will be performed using equipment conventionally and safely used for vascular disease diagnostics and routinely used during vascular and orthopaedic operations. Control participants will receive standard care and no sham treatment (repeated cuff inflation at lower pressure) so as to avoid any detrimental impacts of isolated venous occlusion. Participants will thus not be blinded in the study. However, this is unlikely to introduce bias to the objective measures as muscle and arterial ultrasound images will be anonymised and analysed blinded to subject identity, study time points and group allocation.

The tolerability of RVOS cannot be assessed when participants are ventilated and sedated. Even when participants are extubated and off sedation, delirium (an acute brain dysfunction) is common in critically ill patients and can influence the VAS score. CAM-ICU assessment will be performed and the mental state of the participant during the RVOS session will be recorded to observe any effects of delirium on the VAS score.

Ultrasound assessments of muscle mass and quality and arterial function can be performed when participants are sedated; however, muscle strength and physical function measures are volitional assessments and require the participant’s full attention and cooperation. Therefore, sedation, lack of willingness to participate or lack of mental capacity due to delirium can prevent these outcome assessments. These measures will therefore only be performed when the participant is off sedation and CAM-ICU negative; this could lead to the time points when the strength and physical function assessments are performed varying between participants.

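### The ±15.9% precision for RVOS delivery failure uses all 32 participants; on the 16 planned for the intervention arm it is about ±22.5%

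*Protocol article*

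**What the plan says.** The Sample size rationale first cites a recommendation of 30 participants for pilot and feasibility trials. It then says that, for balance on the stratification factors, "a sample size of 32 participants was chosen". It adds that this number will allow the trial to "estimate a failure to deliver RVOS in the intervention arm of 30% to within a 95% confidence interval of" ±15.9%.

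Other parts of the article fix how many participants can contribute to that proportion:

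- Sample size rationale, next paragraph: "Recruitment will continue until 32 ICU survivors have been studied (16 patients in each group").
- Recruitment and randomisation process: patients are "randomised to either the intervention arm or the control arm in a 1:1 ratio".
- Study design: "Patient randomised to the control arm will receive standard care, while intervention patients will receive RVOS treatment in addition to all other standard care".
- Discussion: "Control participants will receive standard care and no sham treatment".

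**The concern.** Failure to deliver RVOS can occur only in a patient assigned to RVOS, and the sentence itself places the proportion in the intervention arm. The number in that sentence nevertheless looks like one calculated on both arms together.

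This is the only quantitative precision claim offered for the sample size. Delivery of the intervention is also one of the feasibility criteria in Table 3, and the Discussion makes a larger trial conditional on feasibility. A reader who accepts ±15.9% would think that an observed failure of 30% rules out failure in half of patients, since the upper limit would be 46%. On 16 patients the upper limit is about 52%, so it does not.

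**Working it through.** **Inputs from the article**

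- Anticipated failure p = 0.30, in the intervention arm; 95% confidence, taken as two-sided (z = 1.96); stated half-width 15.9 points; total 32; 16 ICU survivors per group (all from Sample size rationale).
- Allocation 1:1 (Recruitment and randomisation process).
- Controls receive standard care and no sham (Study design; Discussion).
- 30% deaths before trial completion, and 47 patients expected over 16 months (Sample size rationale).

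**Formula.** Half-width = z × √(p(1 − p)/n), with p(1 − p) = 0.3 × 0.7 = 0.21.

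**Step 1: reproduce the stated figure.** With n = 32: 1.96 × √(0.21/32) = 0.1588, which rounds to 15.9%. Solving back, n = 1.96² × 0.21/0.159² = 31.9. The denominator was the whole trial.

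**Step 2: use the intervention arm.** With n = 16: 1.96 × √(0.21/16) = 0.2245, or ±22.5 points. Halving n doubles the variance and widens the interval by √2 = 1.41, that is, by 41%.

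| Denominator | Half-width (points) | Interval around 30% |
|---|---|---|
| 32 (as stated) | 15.9 | 14.1% to 45.9% |
| 16 (intervention arm) | 22.5 | 7.5% to 52.5% |

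**Step 3: would another interval method at n = 16 give 15.9?** At p = 0.30 and 95% two-sided confidence, the half-widths are: Wilson 20.5, Clopper-Pearson 23.6, t-based 24.4, continuity-corrected 25.6. A one-sided 95% bound gives 18.8. None gives 15.9.

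**Step 4: count intervention patients who die in the ICU.** Assume that all of the 30% mortality falls in the ICU. Then 16 survivors correspond to 16/0.7 = 22.9, about 23 patients randomised to RVOS. The half-width is 1.96 × √(0.21/23) = 0.187. Half of the 47 expected patients is a similar number; with 24 the half-width is 18.3 points. Both are wider than 15.9.

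**Step 5: what ±15.9 would require.** From step 1, about 32 patients in the RVOS arm alone, which means 64 in total under 1:1 allocation.

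**The case against.** Nobody can put 32 patients in the RVOS arm, so the slip itself is not in dispute. The objections concern its size and its weight.

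- **The 16 are ICU survivors, not everyone who receives RVOS.** This stands. Sessions start on day 1, so patients who later die can also receive RVOS or fail to receive it. Counting them brings the half-width down to about 18.3 to 18.7 points. That shrinks the discrepancy but does not remove it, and the article ties its precision statement to the sample of 32, not to a larger number randomised.
- **Table 3 measures delivery per session, not per patient.** This also stands in part. Sessions are clustered within patients, and the article gives no within-patient correlation. Assume 16 patients with all 19 sessions each (1 + 2 × 9), or 304 sessions. The half-width then runs from 5.2 points with no correlation to 22.5 with full correlation. It equals the stated 15.9 at a design effect of 304/32 = 9.5, a correlation of (9.5 − 1)/18 = 0.47. So session-level precision could fall on either side of ±15.9, and ±22.5 is the per-patient figure only. This does not rescue the printed number: 32 is not a count of sessions, and the match at n = 32 shows that a simple per-patient formula was used.
- **The figure did not drive the sample size, and nothing depends on it.** Largely right. The size rests first on the cited recommendation of 30, and the precision is given as a consequence. The delivery criterion in Table 3 is a bare 80% of sessions with no confidence limit, the analysis is described as exploratory, and recruitment is complete. This limits the consequence, but the statement is still wrong.

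**Conclusion.** The concern holds. The stated ±15.9 points uses both arms as the denominator for a proportion that exists in one arm only. On the 16 patients planned for that arm the half-width is about ±22.5 points (normal approximation, p = 0.30, one binary result per patient). It is about ±18.3 to ±18.7 if 23 to 24 patients are counted because ICU non-survivors are included. No reading of the planned numbers gives ±15.9 per patient. Precision for the session-based criterion cannot be fixed from the article. The statement needs correcting, but its effect on the trial is modest: sample size, design and main analyses are untouched, and no stopping or progression rule shown uses the figure.

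**What to change.** Restate the sentence in the Sample size rationale for the intervention arm, for example: with 16 participants in the RVOS arm, a 30% failure of delivery would be estimated to within about ±22.5 percentage points (95%, normal approximation). If all patients randomised to RVOS are the intended set, say so and give the half-width for that number.

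When the result is reported, use the intervention-arm denominator. A per-patient proportion is best given with an exact or Wilson interval because the number is small. As an illustration, 5 failures in 16 (31%) has an exact 95% interval of 11% to 59% and a Wilson interval of 14% to 56%. If delivery is reported per session, as Table 3 defines it, the interval should allow for clustering within patients.

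The cost is one corrected figure and a less favourable stated precision. The sample size does not change, and since recruitment is complete the correction affects only the text and the reporting.
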